#### Sample Description

Figure 1 presents the sample description in terms of gender, age, and mental distress. We aim for a quota sample of Android smartphone users from the general population. Quota sampling is a form of non-random sampling which approximates population representativeness according to a set of pre-defined criteria, while allowing for participants to self-select into the study (41). Compared to random sampling or stratified sampling, quota sampling is advantageous for the present project due to lower costs, and because smartphone users need to be pre-screened according to psychological distress.

**Figure 1 F1:**
[figure not shown]
Study flow.

Three equally sized distress groups are formed, with inclusion probabilities according to prevalence estimates for the Kessler K6 screening scale (32). To achieve equally sized distress groups, participants with moderate to high distress will be over sampled. To approximate representativeness for the general adult population from 18 to 45 years, quotas for age and gender are defined according to the distribution of the latest Zensus population survey (36). Stratification by age is important to account for differential smartphone usage by age, with younger people having a higher rate of smartphone usage as compared to older people. Three age groups will be formed: Young (18–26, 29,5%), Middle (27–35, 30,1%), and Older (36–45, 40,5%). Due to a higher prevalence of mental health problems among women, groups will also be stratified by gender (49.8% male, 50.2% female).

#### Inclusion Criteria, Informed Consent, and Randomization

The inclusion criteria are age between 18 and 45 years and ownership of an Android smartphone (Android Version 4.0 or higher) with an active internet connection. Exclusion criteria are the presence of suicidal thoughts as measured by one item on the presence of suicidal thoughts, and failure to provide informed consent.

Upon registration, participants will be informed about the requirements and procedure of study on the study website. Additionally, an information booklet with details on the study procedure will be available for download. Informed consent will be obtained of each participant with a written signature when first using the smartphone application. To randomize participants to study conditions, a computerized block randomization procedure will be used (Allocation ratio 1:1:1, block size 10). The researcher preparing the randomization procedure will have no information about participants and will not participate in the recruitment, enrollment of participants, or assignment of participants to study groups.

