## Material and Equipment

### Stepwise Procedures

A fully mobile 3-arm RCT will be conducted. The intervention will be compared toward AAs (self-monitoring without support) and a passive control group (no self-monitoring and no support). We hypothesize that using the intervention will improve mental health as compared to the control groups, where we expect no significant changes. The RCT will be registered prospectively as a clinical trial in the German registry for clinical trials (Deutsches Register Klinischer Studien).

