#### Sample Size Calculation

A power analysis was performed to detect a group difference on the primary outcome at post-assessment group. The calculation is based on the assumption that a difference between the supported monitoring group and either AA group or control group within the margin −0.25 < Cohen’s *d* < 0.25 can be neglected. We assume no difference between the two latter groups. Therefore, a between-group difference of *d* = 0.25 should reach statistical significance as an indicator of the general effectiveness of the intervention. The target sample size was computed using Gpower (40) for a repeated-measures analysis of variance for a within-between interaction of time and group (ANOVA). We used a targeted power of 95%, a significance level alpha of 0.05, four assessment waves, a conservative estimate of correlation between measurements (*r* = 65) and variances of the differences between groups (non-sphericity correction epsilon = 0.8). This results in a total *N* = 141. Adding 20% drop-out at T2 and T3, we will include 186 participants (62 per group).

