*Differential effectiveness*: to examine person-level moderators of the intervention effect, a between-person factor is added to the MANOVA. This results in a three-way interaction (person factor × time × group). However, as only categorical person variables can be included in the MANOVA, multivariate multilevel models for fixed occasions will also be performed to allow for continuous variables as moderators (105). The between-person moderators to be included in the analysis of differential effectiveness include gender, age, and baseline distress severity (low, moderate, high).

Conditional effectiveness: to examine whether time-varying characteristics of the situation (e.g., days spent at work) or the individual (e.g., being physically active) might moderate the intervention effect, multivariate multilevel models will be extended with a continuous or categorical day-level variable. To estimate the pure within-person effect of the time-varying moderator, continuous day-level variables will be centered on the person-mean.

*Effect sizes*: Cohen’s *d* will be calculated as a measure of the effect size, where *d* = 0.8 or more is classified as a large effect, *d* = 0.5–0.8 is classified as a moderate effect, and *d* = 0.2–0.5 is classified as a small effect. According to Feingold (106), the raw score standard deviation of the outcome variable at baseline assessment will be used to compute Cohen’s *d*.

*Treatment response*: changes in mental health on an individual level will be examined with the widely used Reliable Change Index (RCI) by Jacobson and Truax (107). Participants with an RCI greater than 1.96 will be classified as “responders,” and those with an RCI below −1.96 will be classified as “deteriorated.” To assess the average number of persons who need to be treated to prevent one additional bad outcome, the number needed-to-treat (NNT) will be calculated. Additionally, the number-needed-to-harm (NNH) will be calculated, indicating the number of responders in the intervention group for one extra person to have a symptom deterioration. To set the benefits of the intervention in relation to its risk, the benefit-risk ratio will be calculated by dividing the NNT through the NNH (108).

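### A block size of 10 is incompatible with the stated 1:1:1 allocation to three arms

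*Protocol article*

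**What the plan says.** Under Stepwise Procedures the protocol article announces: "A fully mobile 3-arm RCT will be conducted". Under Inclusion Criteria, Informed Consent, and Randomization it fixes the method: "a computerized block randomization procedure will be used (Allocation ratio 1:1:1, block size 10". That section gives no rule for sharing ten places among three arms and names no stratification factor. Under Sample Size Calculation the target is equal arms: "we will include 186 participants (62 per group".

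Two other sections bear on the optional part of this point. Under Sample Description the sample is built on K6 severity: "Three equally sized distress groups are formed". The same section speaks of stratifying by age and gender ("groups will also be stratified by gender (49.8% male, 50.2% female"), but in text about sampling quotas, not about allocation to arms. Under Statistical Analysis (differential effectiveness) the planned moderators "include gender, age, and baseline distress severity (low, moderate, high".

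**The concern.** A permuted block delivers its ratio only if its size is a multiple of the sum of the ratio's terms. For 1:1:1 that sum is 3, and 10 is not a multiple of 3. Whoever programs the list must therefore either change one of the two stated parameters or invent a rule for the surplus place. Different programmers could produce lists with different real ratios, each claiming to follow the protocol.

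At stake are arm sizes and the accuracy of the reported method. There is no bias in the treatment comparison: allocation is still random under any of these rules.

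A secondary matter is balance on baseline distress. It shapes the sample and is a planned moderator, but the randomisation text does not mention it.

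**Working it through.** **Inputs.** Three arms (Stepwise Procedures); ratio 1:1:1 and block size 10 (Randomization section); N = 186 with 62 per arm (Sample Size Calculation); three equal distress groups (Sample Description), so 186/3 = 62 participants each.

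**The plan's own figures.** 3 × 62 = 186, so the total and the arm sizes agree with each other and with 1:1:1. The block size does not: 10 = 3 × 3 + 1, which leaves one surplus place in every block.

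**Where the surplus goes.** 186 = 18 × 10 + 6, so the list runs through 18 full blocks and 6 places of a nineteenth. Each rule was simulated 5,000 times to N = 186. The gap is largest arm minus smallest arm.

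| Rule for the tenth place | Mean arm sizes | Median gap | 95th percentile of gap |
|---|---|---|---|
| Always the same arm | 74.4 : 55.8 : 55.8 | 19 | 21 |
| Drawn at random in each block | 62 : 62 : 62 | 4 | 9 |
| Rotating over the arms | 62.4 : 61.8 : 61.8 | 2 | 3 |

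Hand checks:
- Same arm: 18 × (4, 3, 3) = (72, 54, 54). The last six places add on average 6 × 0.4 = 2.4 and 6 × 0.3 = 1.8 twice, giving 74.4 : 55.8 : 55.8.
- Rotating: after 18 blocks each arm has 18 × 3 + 6 = 60, so only the incomplete last block causes any gap.
- Random: the surplus count per arm has SD √(18 × 1/3 × 2/3) = 2.

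**Cost of the worst case.** For the three-group comparison, the harmonic-mean arm size at 74:56:56 is 3/(1/74 + 2/56) = 60.9, against 62. The loss is 1 − 60.9/62 = 1.8%, under 2%. A pairwise comparison between the two smaller arms would have 56 instead of 62 per arm (56/62 = 0.90).

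**Block sizes that fit.** Any multiple of 3 is compatible with 1:1:1. Of the multiples up to 30, only 3 and 6 also divide 186 (62 and 31 blocks), so fixed blocks of either size end at exactly 62:62:62. Blocks of 9 or 12 end with a gap of at most 3 or 4.

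**Distress groups, if allocation is not stratified.** With arms of 62, the number of the 62 high-distress participants in one arm is hypergeometric:
- mean = 62 × 1/3 = 20.7
- SD = √(62 × 1/3 × 2/3 × 124/185) = 3.04
- approximate 95% range = 20.7 ± 1.96 × 3.04, about 15 to 27

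Simulated with unstratified blocks of 6, the high-distress count differs between the largest and smallest arm by a median of 6 (95th percentile 12).

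**The case against.** The strongest reply is that this is a slip of little consequence. If the surplus place is random or rotates, the arms end close to 62 each. Even if it always goes to one arm, the three-group test loses under 2% in effective arm size and nothing is biased. All of that stands, and it limits the weight of the point. It does not remove the contradiction: the sentence cannot be followed as written.

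The 10 might also mean ten per arm, that is, a block of 30. That would restore 1:1:1, and since 186/30 = 6.2 the incomplete last block would leave a gap of at most 6. But the text calls 10 the block size, so the sentence would need correcting under this reading too.

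Three stronger readings are tempting and are not supported:
- **That the trial will run at 72:54:54 over the full blocks.** This needs the surplus always to fall to the same arm, which the article does not say.
- **That 186 not being a multiple of 10 is a second error.** An incomplete last block is routine.
- **That randomisation ignores the distress groups.** A reader might infer this because the randomisation section names no stratum. But the article is condensed, and the study-flow figure, which could show where allocation sits relative to the distress groups, is not available here. Silence does not establish an unstratified list. Nor does the article rank distress as a predictor of outcome. Unstratified randomisation would be valid in any case, with chance imbalance already allowed for in the test and distress modelled as a moderator.

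**Conclusion.** The stated block size and allocation ratio contradict each other, and this follows from the article alone without any assumption. The size of the consequence does rest on an assumption, namely the unstated rule for the tenth place. It ranges from a real ratio of 4:3:3 (about 74:56:56) to arms that typically differ by only 2 to 4 participants. Validity is not threatened and the loss of power is small in all cases. The point should still be settled because the method is wrong as written and recruitment has not begun (Trial Status).

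Stratifying by distress is a possible gain in balance for the distress-by-arm cells, not a correction of an error. The figures given for it apply only if allocation is not already stratified.

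**What to change.** Replace the block size of 10 with a multiple of 3. Fixed blocks of 3 or 6 give exactly 62:62:62 at 186; randomly varying sizes such as 3, 6 and 9 also keep 1:1:1, with a small possible gap at the end of the list. If blocks of 30 were meant, say so. The cost is one parameter in the randomisation program and one corrected sentence, with no additional participants.

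Optional: state whether allocation is stratified by the three K6 distress groups. If it is not, generating the blocks separately within each group would even out the distress-by-arm cells. The price is small: 62 is not a multiple of 3, so each stratum ends in an incomplete block and overall arm sizes may differ slightly from 62.

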#### Additional Procedures

*Telephone reminders*: to limit study drop-out, telephone reminders will be initiated in the case of failure to respond to an outcome assessment or failure to download the smartphone application. The study team will constantly supervise enrollment, downloads of application, and compliance with the study protocol, and will initiate telephone calls to participants that need to be reminded.

*Application reminders*: to increase adherence and to stimulate user engagement with the intervention, push notifications on the Android device will remind participants to complete the daily self-monitoring report and will remind users to engage with intervention content, e.g., by displaying a notification that a new daily health tip is available.

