### Limitations

The proposed study has several limitations. First, short screening scales for mental health will be used (self-reports on the device and assessed by telephone interview), but due to feasibility limitations and to minimize participant burden, no diagnostic interview on mental disorders can be conducted (e.g., according to DSM-V).

Second, as participants will self-select themselves into the study, there is potential selection bias. We cannot exclude the possibility that the participants who enroll in the study have certain characteristics that differentiate them from the target group. This means that the generalizability of results is limited to smartphone users who select themselves into using the intervention. However, quota sampling according to age and gender will ensure that the sample will be representative for the population in regard to these characteristics.

Third, potential low response and loss to follow-up present a challenge for this study. Low response/retention rates would reduce the statistical power and can generate a selection bias which affects the generalization of the results. This risk needs to be carefully considered during designing and planning of the study. We will conduct telephone reminders to enhance response. To prevent systematic low response and follow-up loss among hard-to-reach populations, study staff will carefully monitor recruitment rates according to the sample composition in Figure 1: Study flow. Sup-populations showing low response during recruitment will be targeted specifically (e.g., older subjects, male subjects). Using flexible online advertisements, we will place ads that will be shown only to certain sub-populations to enhance response and ensure a representative composition of the sample.

Fourth, potential “gaming” needs to be avoided, which refers to a situation where research participants fraudulently enroll in a study for the purpose of acquiring research payment. Procedures to prevent gaming will include locking the registration procedure in case of participants trying to change submitted answers, availability of study links only for one user/device, and tracking of IP addresses to prevent duplicate enrollment.

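### One fixed, published block size of 10 leaves the ends of blocks deducible for anyone who learns past assignments, and it cannot be split 1:1:1

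*Protocol article*

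**What the plan says.** All references are to the protocol article.

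- **Allocation** (Inclusion Criteria, Informed Consent, and Randomization): "a computerized block randomization procedure will be used (Allocation ratio 1:1:1, block size 10". No variation in block length is mentioned.
- **Stated safeguard** (same section): "The researcher preparing the randomization procedure will have no information about participants", and that researcher takes no part in recruitment, enrolment or assignment. Nothing comparable is said of the staff who do those tasks.
- **What the team follows** (Additional Procedures): "The study team will constantly supervise enrollment, downloads of application, and compliance with the study protocol". The team also telephones people who have not downloaded the app.
- **Blinding** (Outcomes): only the telephone interviewers are described as blinded to condition.
- **Arms** (Control Groups): supported monitoring, daily assessments without support, or neither.
- **Quotas** (Limitations): "study staff will carefully monitor recruitment rates according to the sample composition in Figure 1". Under-filled groups are reached through targeted advertisements.
- **Size** (Sample Size Calculation): "we will include 186 participants (62 per group".

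**The concern.** Within a permuted block of known length, the last places can be worked out from those already used. Keeping the list preparer away from participants protects the list before use, but it does not prevent deduction from assignments already made. Daily monitoring exists in only two arms and supportive feedback in only one, so a team that supervises compliance will plausibly learn who is in which arm.

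If someone who can influence a person's entry or its timing also knows the next arm, the arms may differ at entry. Blinded K6 interviews protect the measurement of the outcome, not the composition of the arms. Separately, ten places cannot be divided 1:1:1, so equal arms are not secured by the blocks themselves.

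**Working it through.** **Inputs.** From the article: block size 10, ratio 1:1:1, 186 participants, 62 per group (3 × 62 = 186). The article gives no figure for predictability, so there is none to reproduce. Assumptions: one unstratified list, each block split as nearly equally as possible (10 = 4 + 3 + 3), and an observer who knows all earlier assignments in order.

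**Formula.** If the block's composition is known, an assignment is certain when only one arm remains, that is, during the final run of one arm. For an arm with n of N places, the chance that the last j places are all that arm is n(n−1)…(n−j+1) / [N(N−1)…(N−j+1)]. Summed over j, this gives n/(N−n+1). The expected number of certain assignments per block is the sum over the arms.

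**Extra arm known (4:3:3).** 4/7 + 3/8 + 3/8 = 1.321 of 10, or 13.2%.

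**Extra arm random and unknown.** A final run of the four-place arm is never certain, because the observer cannot tell where the extra place lies. What remains is 3/8 + 3/8 = 0.75 of 10, or 7.5%.

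**Over 186.** There are 18 full blocks plus six places, and no assignment among those six can be certain.
- Random extra arm: 18 × 0.75 = 13.5, or 7.3%.
- Known extra arm: 18 × 1.321 = 23.8, or 12.8%.

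**Other reading.** If 10 means ten per arm, the block is 30 and the figure is 3 × 10/21 = 1.429 of 30, or 4.8%. A block of 30 also divides by three.

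**Arm sizes with blocks of 10.** If the same arm always has the extra place, 18 blocks give 72/54/54 before the last six people, which cannot end at 62 each. Rotating the extra place gives 60/60/60 before the last six. If it falls at random, each arm receives on average 6 of the 18 extra places, with SD √(18 × 1/3 × 2/3) = 2.

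**Alternatives.** The fixed designs are exact. The varied designs are simulated (400 trials of 186; the observer knows the set of lengths but not their order).

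| Design | Certain | Best guess correct |
|---|---|---|
| Fixed 10, extra arm random | 7.3% | 48.3% |
| Fixed 10, extra arm known | 12.8% | 53.6% |
| Varied 3/6/9 | 3.9% | 55.4% |
| Varied 6/9 | 5.2% | 54.2% |
| Varied 6/9/12 | 2.5% | 52.8% |

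Chance is 33%. A fixed block of 9 has 3 × 3/7 = 1.286 certain assignments of 9, or 14.3%. Making the block divisible by three therefore does not reduce predictability; varying the length does. With 6/9/12, about 0.025 × 186 = 4.6 assignments remain certain.

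**The case against.** The strongest reply is that selection bias needs staff who both know the next arm and control who takes it, and the article shows neither.

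- **Control.** People register and screen themselves on a website, and allocation is computerized. The quota lever described is advertising, which does not pick the next registrant. Calls about missing downloads do act on individuals, and consent is signed at first use of the app, but the article does not say whether allocation comes before or after that step. If it comes before, the calls cannot steer it.
- **Visibility.** Nothing says that the team sees assignments in order. A download alone does not reveal the arm, because all three groups complete secondary outcomes on the smartphone.
- **The 13% case.** It needs a known extra arm. A constant one conflicts with 62 per group, and no rotation is described.
- **The remedy.** Average guessing does not improve, and against the random-extra-arm case it is slightly worse (52.8% against 48.3%).

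All of this stands, and it sets the limits of the point. A reader might infer that the staff who fill the quotas can know 7–13% of assignments in advance; the article does not support that. A reader might also turn the percentages into a bias in SD units and set it against the plan's d of 0.25. That would assume steering that is nowhere described, and it would overlook that the planned test is the time-by-group interaction, which concerns change rather than the level at entry.

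What the reply does not remove is that the block length is fixed and printed, that only the interviewers are stated to be blinded, and that the stated separation covers only the list preparer.

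**Conclusion.** The point holds as an avoidable weakness in concealment, not as a demonstrated bias. At most about 7% of assignments (about 14 of 186) would be certain to an observer who tracks every assignment when the extra place falls at random. The share rises to 13% only if the extra arm is known, and is 4.8% if 10 means ten per arm. These bounds rest on one unstratified list and 4:3:3 blocks. The article mentions stratification by age and gender when it describes the sample, but does not say whether this applies to the randomization.

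Read as a total block length, 10 is also incompatible with the stated 1:1:1 ratio, whatever anyone can observe.

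**What to change.** In the randomization paragraph, replace the block size of 10 with: *permuted blocks of randomly varying length in multiples of three (e.g. 6, 9 and 12), with lengths withheld from staff involved in recruitment, enrolment and reminders; the computerized procedure releases each assignment only after eligibility and consent are recorded.*

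Against the random-extra-arm case this removes about 9 of the 13.5 certain assignments, and every completed block is balanced 1:1:1. It leaves the average best-guess rate at about 53%. If recruitment stops inside a block of 12 (4/4/4), two arms can differ by up to four participants. The work is a change of program settings and a sentence or two of text, and the Trial Status section places the trial still in preparation.
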